### Criteria

Inclusion criteria:
Patient agrees to cooperate with all study procedures;Age > 20 years old;Physical status permits oral medication;Cholesterol < 5.1 mmol/l, triglyceride < 1.7 mmol/l;Provision of written informed consent.

Exclusion criteria:
Liver dysfunction: alanine aminotransferase (ALT)/aspartate aminotransferase (AST) > 3 times the normal value;Breast-feeding or pregnancy (for women of child-bearing age, the human chorionic gonadotropin level will also be measured before drug administration);Previous history of coronary atherosclerotic heart disease;Statins used within 6 months before inclusion;Participation in another clinical trial within 6 months;Allergy to statins.

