### Statistical and analytical plans

A comprehensive statistical analysis plan will be prepared before database locking. All analyses will be conducted according to the intention-to-treat (ITT) principles. The primary outcome is binary, it will be expressed as frequency and percentage, a chi-square test will be used to analyze. All statistical analyses will be two-sided, and statistical significance will be set at 0.05. Continuous data such as blood pressure, heart rate and blood parameters, will be presented as mean ± SD; Categorical data, such as previous disease history and smoking history, will be expressed as frequency and percentage of patients in each category. The Kolmogorov-Smirnov test will be used to confirm the normality of the distribution of continuous data, if *P* < 0.05 indicates the data is not normally distributed, advanced raw data conversion (such as logarithmic conversion) will be performed to see whether the data conform to a normal distribution. If not, the rank-sum test will be selected. Otherwise, Student’s *t* tests will be used for continuous data. The chi-square test will be used for categorical data. Survival curves will be determined by the Kaplan-Meier method for survival analysis. The difference in changes between the groups will be analyzed using both Student’s *t* test and analysis of covariance to adjust for the baseline values. A *p* value of < 0.05 will be used to indicate statistical significance. The missing data will be handled by using Mean/Mode Completer. If the missing data is numerical, it will be filled according to the average value of all other objects; if the missing data is non-numerical, then it will be supplemented by the value with the most frequent value of all other objects according to the mode principle in statistics. SPSS statistical software (SPSS Inc., Chicago, IL, USA, version 23) will be used for statistical analysis.

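### Changes in laboratory and vital-sign measures get two tests at 0.05 with neither leading, and a normality test picks the method for continuous data; ANCOVA alone on a pre-set scale is better

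*Protocol article*

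**What the plan says.** All of this stands in the protocol article, Statistical and analytical plans, unless another section is named.

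- **Two tests of change.** "The difference in changes between the groups will be analyzed using both" Student's t test and "analysis of covariance to adjust for the baseline values". No order is given, and no rule covers disagreement.
- **Significance level.** "All statistical analyses will be two-sided, and statistical significance will be set at 0.05". Each test therefore carries the full 0.05.
- **Normality gate.** "The Kolmogorov-Smirnov test will be used to confirm the normality of the distribution of continuous data", with P < 0.05 as the cut-off. After a rejection, "advanced raw data conversion (such as logarithmic conversion) will be performed to see whether the data conform to a normal distribution". Then: "If not, the rank-sum test will be selected". Otherwise a t test is used.
- **Summaries.** Continuous data are presented as mean ± SD, and the section gives no alternative for variables that end in a rank test.
- **Measures concerned.** Blood pressure, heart rate and the blood parameters. The eleven blood parameters are taken at baseline, day 7 and day 13 (Data collection and management).
- **Not concerned.** The primary outcome, in-hospital mortality at 30 days, is binary and has a chi-square test. The secondary outcome is the incidence of liver dysfunction (Outcome measurements), which is also binary.

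**The concern.** Two p-values for the same question, each at 0.05, leave the reader or the author free to take the one that is significant. The change-score t test and ANCOVA are correlated but not identical, so they will sometimes disagree, and the protocol has no rule for that case. The t test also brings nothing that ANCOVA lacks. In a randomised trial both estimate the same treatment difference, and ANCOVA does so with equal or smaller variance.

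The normality gate is a separate weakness. A difference in means, a difference on the log scale and a rank comparison answer different questions. If a p-value chooses among them variable by variable, CRP at day 7 and CRP at day 13 may be analysed on different scales, and a rank-sum p-value may be printed next to means and SDs that it does not test.

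At stake is the clarity of the exploratory evidence on inflammation, lipids and continuous liver enzymes, not the trial's main conclusion.

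**Working it through.** **Inputs from the protocol.** Two-sided alpha 0.05 for every analysis; two tests per change; 192 per arm. The protocol gives no figure for the continuous measures. Its sample size, which supplies the 192, reproduces:
- Hazard ratio = ln(1 − 0.124)/ln(1 − 0.274) = 0.4135.
- Freedman events = (1.960 + 1.282)² × ((1 + 0.4135)/(1 − 0.4135))² = 61.0.
- N = 2 × 61.0/(0.274 + 0.124) = 306.6, rounded up to 307.
- 307/0.8 = 383.75, rounded up to 384, or 192 per arm.

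**Assumption.** The correlation ρ between baseline and follow-up is not in the protocol. I take 0.2 to 0.8, with equal variances at the two times.

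**Step 1: precision.** With unit variance at each time, the change score has variance 2(1 − ρ) and the ANCOVA residual has variance 1 − ρ². The ratio is (1 − ρ²)/(2(1 − ρ)) = (1 + ρ)/2.

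**Step 2: false positives if either test counts.** Under no treatment effect the two test statistics have correlation √((1 + ρ)/2). The chance that at least one exceeds 1.96 in absolute value follows from the bivariate normal distribution. The chance that both do is 2 × 5% minus that figure.

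| ρ | ANCOVA variance / change-score variance | Correlation of statistics | Either significant | Both significant | Share of false positives on one test only |
|---|---|---|---|---|---|
| 0.2 | 60% | 0.775 | 8.0% | 2.0% | 74% |
| 0.4 | 70% | 0.837 | 7.6% | 2.4% | 68% |
| 0.6 | 80% | 0.894 | 7.1% | 2.9% | 59% |
| 0.8 | 90% | 0.949 | 6.5% | 3.5% | 46% |

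Simulation with 192 per arm and 6,000 runs per setting, at ρ of 0.3 to 0.7, gives 6.6% to 7.6% for either test. ANCOVA alone gives 4.5% to 5.1%.

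**Step 3: what the weaker test costs in power.** For an assumed true difference of 0.3 SD with 192 per arm, power of the change-score t test against ANCOVA is 70% against 87% (ρ 0.3), 84% against 92% (ρ 0.5) and 97% against 98% (ρ 0.7). These are upper figures: the average stay was 13 days (Follow-up), so fewer than 192 per arm may have a day-13 value.

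**Step 4: the normality gate.** The same simulations applied the route of t test, then log scale, then rank-sum to the changes, using the Kolmogorov-Smirnov test with estimated parameters (Lilliefors).

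| Procedure | Normal data | Skewed (log-normal) data |
|---|---|---|
| Gated test alone | 4.6% to 4.8% | 4.7% to 4.9% |
| Gated test or ANCOVA significant | 6.6% to 7.5% | 7.9% to 8.4% |

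The gate alone holds the nominal level. The excess comes from running two tests; the gate adds about one percentage point to it, and only for skewed data.

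**Step 5: does the gate reject baseline lipids by construction?** Entry requires "Cholesterol < 5.1 mmol/l, triglyceride < 1.7 mmol/l" (Criteria), so baseline values are cut off. Cholesterol was simulated as a normal distribution truncated at 5.1, n = 190. The mean and SD before truncation are assumptions.

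| Assumed mean / SD | Raw values rejected (Lilliefors) |
|---|---|
| 4.6 / 0.9 | 95% |
| 4.0 / 0.9 | about 47% to 49% |
| 4.0 / 0.7 | about 21% to 22% |
| 3.8 / 0.8 | 17% |

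Without the correction for estimated parameters, the 4.6 / 0.9 case is rejected in only about a quarter of samples. The protocol does not say which version applies. The route taken therefore depends on unknown distributions and on an unspecified version of the test.

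**The case against.** **The analysis plan can settle this.** The protocol promises a comprehensive statistical analysis plan before database lock, and the lead analysis of exploratory measures is often named there. That stands for details such as which laboratory values are logged. It does not fully answer the point, because the protocol does not leave the choice open: it fixes both tests. A plan that named one would replace a stated rule.

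**ANCOVA is already there.** An unadjusted result printed beside it takes no precision away from the ANCOVA estimate, and the inflation arises only if either p-value is read as decisive. Both parts are true. The inflation figures are conditional on that reading, which the protocol neither endorses nor rules out.

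**The gate is not said to precede the change analysis.** The protocol sets out the Kolmogorov-Smirnov route for continuous data in general, and names the t test and ANCOVA for changes some sentences later. Applying the gate to changes is a natural reading, not an explicit one. This stands, so the gate is treated here as a separate point.

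**Stronger readings that the document does not support.** A reader might infer that the normality pre-test itself inflates false positives; the simulations put it near 5%. A reader might infer that truncated lipids must fail the normality test; for raw cholesterol the rejection rate ranges from about 17% to 95% with the assumed distribution, and the cut-offs apply to baseline values, not to changes. A reader might also infer that the liver-safety conclusion rests on these tests; that outcome is an incidence and falls under the chi-square test for categorical data.

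**Conclusion.** The point holds in a limited form. The protocol fixes two analyses of the same change, each at 0.05, and names no lead. Counting either as a finding gives about 8.0% to 6.5% false positives per measure for ρ of 0.2 to 0.8, under equal variances at the two times. The extra test is the less precise one throughout that range.

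The normality gate is a fault of interpretation rather than of error rate: the scale may vary between variables and visits, and p-values may not match the means reported beside them.

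No stated primary or secondary outcome is affected. This is a free improvement of low severity, confined to exploratory laboratory and vital-sign measures.

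**What to change.** Replace the sentences on the normality test and on changes with wording such as:

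*Each day-7 and day-13 continuous measure will be compared between groups by ANCOVA, adjusted for the baseline value and for dissection type (A or B), and reported as an adjusted mean difference with 95% confidence interval. CRP, ALT and AST will be analysed on the log scale. Residuals will be inspected graphically. No normality test will determine the analysis.*

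Drop the change-score t test. The list of logged variables is an example; what matters is that it is fixed before outcome data are examined. Summaries should follow the chosen scale, for instance geometric means for logged variables. Dissection type belongs in the model because it is the randomisation stratum (Randomization and allocation).

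The cost is wording only. Baseline values are already collected, dissection type is known at randomisation, and ANCOVA is already planned. The change can go into the statistical analysis plan before database lock, with a protocol amendment so that the two documents agree. All that is lost is a redundant p-value.

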### Monitoring

This study will be performed in accordance with the approved protocol. The data and safety monitoring committee of the First Affiliated Hospital of Shantou University Medical College will review and interpret the data generated from the study in order to ensure the safety of the participants and the integrity of the research data. The committee consists of five independent researchers who are independent of the funders and have no conflict of interest with this study. The data and safety monitoring committee will review the data after 25%, 50%, and 75% enrollment to monitor the study progress and all adverse events (AEs) that may occur. Computer-generated and time-stamped audit trials will also be implemented for tracking changes in the electronic source documentation to ensure the integrity of the research data.

### Auditing

An audit by the ethics committee’s representatives during the course of the study will be performed according to national regulations. All protocol modifications will be communicated to the relevant parties.

### Safety and adverse events

The most common AEs related to the intake of atorvastatin are expected to be liver enzyme abnormalities, muscle pain, nausea, and diarrhea. Participants showing any adverse event will be treated appropriately by doctors, and the project will cover the cost of adverse events. Adverse reactions will be checked at every visit. For any AE that occurs, all details, including the time of occurrence, symptoms and signs, degree, duration, laboratory findings, treatment, outcomes, and causal relationship with the treatment, will be recorded in the CRF. Serious AEs will be reported to the Research Ethics Committee within 24 h, which will decide whether any additional measures should be taken. The total number of patients with AEs related to the study drug (certain, probable, possible) and the total number of patients with AEs leading to discontinuation of study treatment will be summarized.

### Amendment

All proposed protocol changes will be recorded in a protocol amendment and this will be submitted to the Committee of Ethics and the regulatory authority for approval.

### Limitations

The limitations of this study should also be considered, including confirming that patients can diet normally before being formally included in the study, which may exclude critically ill patients whose deaths would occur within several hours of onset and would not be reported, thereby reducing the mortality rate reported for AAD. For surgical patients, preoperative fasting is often required, and patients in this group often need to wait until a normal diet is restored after surgery before they can be included in the study, which may also exclude critically ill patients whose deaths would occur before normal dieting is restored and would not be reported, thereby reducing the mortality rate reported for AAD. Considering the safety of atorvastatin, a low dose of 20 mg/day will be used in this study, and any possible effects may not be very significant. This is an exploratory study. If there is no significant positive effect at the end, but the results suggest it is safe and does not increase mortality, effectiveness may be observed by subsequently increasing the dose. We will explore the most appropriate dose in the next study. As atorvastatin is a tablet drug, we have sought several companies including Pfizer for suitable tablet placebo, while we failed to find out such placebo that are totally the same in color, shape, smell, and taste. So this is an open-label trial which may weaken its persuasiveness. However, if the results of this study are positive, it will provide evidence in reducing in-hospital mortality in patients with AAD, we will continue to carry out multicenter double-blind study to verify the results of this experiment.

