## Background

Acute aortic dissection (AAD) is relatively uncommon but is considered a life-threatening, potentially fatal condition [1]. A recent International Registry of Acute Aortic Dissection (IRAD) study shows that 87–90% of AAD is treated surgically, and drug treatment only accounts for 7–8%. Nevertheless, the IRAD study indicates that in-hospital surgical mortality for AAD remains approximately 20% [2], indicating improvement of the long-term outcome of patients with aortic diseases requires further optimization [3]. However, in addition to strict control of blood pressure and heart rate, the effect of other drugs on AAD is still controversial and lacking strong clinical evidence.

Dyslipidemia and atherosclerosis are important risk factors for AAD [4]. Lipid deposition in the vascular wall can lead to local inflammation [5] and promote the release of inflammatory mediators that destroy the vascular wall, leading to aortic dissection (AD) [6]. Statins are classical drugs for lowering low-density lipoprotein cholesterol (LDL-C) levels, and are both anti-inflammatory and anti-atherosclerotic [7], suggesting that statins may delay progression of AAD.

Recent reports have shown that statins have anti-inflammatory effects and can decrease morbidity and mortality following surgical repair of aneurysms in patients with abdominal aortic aneurysms and aneurysm expansion [8–11], and several experimental studies demonstrate the protective effect of statins [12–14]. A retrospective study showed that patients with AAD who used statins had a significantly better prognosis than those who did not [15]. Also, a prospective and randomized comparative study of patients with uncomplicated acute type B aortic dissection (ABAD) showed that pitavastatin treatment has a suppressive effect on aortic arch dilatation [3]. However, a retrospective review points out that statins do not improve in-hospital and long-term outcomes in patients with Stanford B aortic dissection treated with endovascular aortic repair [16]. Although these studies have explored the effects of statins on aortic disease [3, 14–17], the results remain controversial. The aim of this randomized clinical trial study is to understand the efficiency of atorvastatin on in-hospital mortality of patients with AAD. We propose that AAD patients treated with statins will have lower in-hospital mortality than patients without.

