### Randomization and allocation

According to the order of the participants enrolled, they will be randomly assigned to the control or statin group by using a corresponding random number and envelope method for allocation concealment (patients will be assigned to a corresponding group according to the allocation sequence in an envelope that will be distributed to the research implementation personnel after the allocation sequences are packed in an opaque envelope by separate staff). Balance in allocation across the study participants will be enhanced through stratification by the type of AAD (two types: type A, type B). To avoid the imbalance caused by simple randomization, we introduce block randomization. The block length was 4 with two groups in this study (statins group and control group). The allocation sequence will be generated at a 1:1 (statin/control) ratio using the random number generator in the SPSS statistical software package (SPSS Inc., Chicago, IL, USA, version 23) (Fig. 1).

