### Interventions

Participants will be randomized into two equal groups: statin (atorvastatin) or control group as soon as clinical conditions permit. The statin group will be required to take atorvastatin 20 mg daily (known to be a safe dose effective in lipid-lowering and anti-inflammatory activity [19–21]), and the control group will be required to not take statins during study period. Atorvastatin will be provided by Pfizer (New York, USA).

The scheduled duration of treatment is the duration of the hospital stay unless a serious adverse event occurs or the participant quits. The detailed study schedule is listed in Fig. 2.

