### Data collection and management

At enrollment, we will collect the demographic information of the participants, including age, gender, blood pressure, heart rate, previous disease history, medical history, smoking history. Leukocytes, hemoglobin, platelets, C-reactive protein, cholesterol, triglycerides, creatinine, uric acid, glycosylated hemoglobin, AST, and ALT will be measured at baseline, the 7th, and 13th day. Here, 2 mL fasting venous blood will be taken for measurement in the morning. All these blood parameters will be collected. At discharge or death of the patient, data will be collected on patient status, medication in the hospital, diagnosis and comorbidity. All data will be transferred to a database by duplicate entry using EpiData software (Denmark, version 3.1), and will be stored in the scientific research platform of the First Affiliated Hospital of Shantou University Medical College, which is a secure server with limited access and supported for anonymity, analysis and review.

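### Patients randomised before or without aortic repair are pooled with patients randomised after it, and neither the stratification, the primary test nor the stated conclusion tells them apart

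*Protocol article*

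**What the plan says.** All references are to the protocol article.

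- **Entry.** The Criteria section requires "Physical status permits oral medication". Interventions has participants randomised to "statin (atorvastatin) or control group as soon as clinical conditions permit", with no limit on time from onset, admission or operation. Limitations adds that for surgical patients preoperative fasting is common and that "patients in this group often need to wait until a normal diet is restored after surgery before they can be included in the study".
- **Surgical share.** Background cites a registry in which "87–90% of AAD is treated surgically, and drug treatment only accounts for 7–8"%. It also says that "in-hospital surgical mortality for AAD remains approximately 20"%.
- **Allocation.** The only stratification factor is dissection type: "Balance in allocation across the study participants will be enhanced through stratification by the type of AAD (two types: type A, type B").
- **Data.** The enrolment list in Data collection and management is given as "including age, gender, blood pressure, heart rate, previous disease history, medical history, smoking history", plus laboratory values. Neither that list nor the list for discharge or death names an operation, its date or the time from onset.
- **Analysis.** Statistical and analytical plans treats the primary outcome as binary and assigns it a chi-square test. No covariate is named for mortality.
- **Claim.** Study objectives and hypothesis, Limitations and Discussion all speak of mortality in AAD patients without restriction. Limitations mentions late entry, but draws only one consequence from it: early deaths are missed, so the reported mortality is lower.

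**The concern.** A patient randomised before or without repair may still have a progressing dissection. A patient randomised after repair, once eating normally, has already survived the operation. The two are likely to differ in remaining risk and in what the drug could still act on. Part of the rationale in Background concerns the disease process itself, "suggesting that statins may delay progression of AAD", and that part bears less directly on a patient whose aorta has been repaired.

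Dissection type may partly track surgical management. It does not show whether repair came before randomisation, since a patient of either type can be enrolled on either side of an operation.

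Two things are at stake:

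- **Meaning of the result.** The result would be presented as the effect in AAD, with no statement of how many participants began treatment after repair. Limitations and Discussion also say that a null but safe result may be followed by a higher dose. Treatment lasts only for the hospital stay, so late entry also shortens exposure. Without entry status in the analysis, a null result from late and short exposure looks the same as one from any other cause.
- **Precision.** If entry status predicts death, an unadjusted test gives up some precision.

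**Working it through.** **1. The plan's own sample size.** Inputs from Sample size: mortality 27.4% and 12.4%, two-sided alpha 0.05, power 90%, Freedman log-rank method, 20% loss.

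- Hazard ratio = ln(1 − 0.124)/ln(1 − 0.274) = 0.4135.
- Events = (1.960 + 1.282)² × ((1 + 0.4135)/(1 − 0.4135))² = 61.02.
- N = 61.02/0.199 = 306.6, so 307, where 0.199 is the mean of the two mortalities.
- 307/0.8 = 383.75, so 384, or 192 per arm.

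The stated figures reproduce, and 384 is used below.

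**2. Share entering after repair.** Share = s × f. Here s is the surgical share (87–90%, the registry figure in Background) and f is the fraction of surgical patients who enter after the operation. The article does not give f; it says only that this happens often.

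| f (assumed) | Share of participants | Of 384 |
|---|---|---|
| 0.50 | 44–45% | 167–173 |
| 0.60 | 52–54% | 200–207 |
| 0.75 | 65–68% | 251–259 |
| 1.00 | 87–90% | 334–346 |

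Post-operative entrants are a majority only if f exceeds 0.5/0.90 = 0.556 to 0.5/0.87 = 0.575.

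**3. What adjustment would gain.** The article gives no mortality by entry status, so two splits are assumed, with the same mortality in both arms. Fraction of outcome variance explained = w(1 − w)(p₁ − p₂)²/[p(1 − p)], where w is the post-operative share and p the overall mortality.

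- **Split A:** 60% post-operative at 8%, 40% otherwise at 30%.
  - p = 0.6 × 0.08 + 0.4 × 0.30 = 0.168.
  - Fraction = 0.24 × 0.0484/(0.168 × 0.832) = 8.3%.
- **Split B:** 50% at 10%, 50% at 25%.
  - p = 0.175.
  - Fraction = 0.25 × 0.0225/(0.175 × 0.825) = 3.9%.

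**4. Chance imbalance, and why it is not a further loss.**

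- Split A: the standard deviation of the between-arm difference in entry status is √(2 × 0.6 × 0.4/192) = 5.0 points. Multiplied by the 22-point mortality gap and 1.96, this gives ±2.2 points.
- Split B: √(2 × 0.5 × 0.5/192) = 5.1 points. With a 15-point gap, this gives ±1.5 points.
- The unadjusted 95% half-width for the mortality difference is 1.96 × √(2 × 0.168 × 0.832/192) = 7.5 points in A, and 7.6 points in B by the same formula.
- (2.2/7.5)² is about 8% and (1.5/7.6)² about 4%, the same fractions as in step 3. The imbalance is therefore already inside the unadjusted standard error.
- Adjustment narrows the half-width from 7.5 to 7.5 × √(1 − 0.083) = 7.2 points in A, and from 7.6 to about 7.5 points in B.

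Any balance that stratification by type already brings is ignored here, so these gains are, if anything, generous.

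**The case against.** The case on the other side is substantial, and much of it stands.

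- **The headcount is not known.** A reader might infer that the trial mainly tests atorvastatin after the operation, with 334–346 post-operative participants. The documents do not support that. The 87–90% is a registry figure, the site's share is not given, and how often patients enter late is not quantified. Surgical patients who die before eating again are never enrolled, which lowers the share further.
- **Late entry is disclosed.** Limitations states it, calls the study exploratory and defers confirmation to a later multicentre double-blind trial. This stands, but the disclosure concerns the reported mortality rate and not which treatment effect is estimated.
- **Post-operative benefit is within the rationale.** Background also cites better outcomes with statins after aneurysm repair, and Discussion relies on inflammation and endothelial function. Pooling is therefore a defensible pragmatic choice and not a contradiction.
- **The data may exist.** The enrolment list comes from a condensed article, and neither the case report form nor the schedule figure is shown. It cannot be said that the analysis would be unable to separate the groups. The absence of the item from the list is weak evidence. The type-only stratification, the chi-square test and the unrestricted claim are printed.
- **Exposure cannot be computed.** A reader might subtract a late entry day from the 13-day mean stay in Follow-up to get a few days of drug. A patient still in hospital late on has already outlasted the short stays, so the subtraction is not valid. The direction (later entry, shorter exposure) holds; a number of days does not.
- **There is no bias.** Both arms enter under one rule before allocation. This stands in full.

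**Conclusion.** The point holds as one of interpretation, with a modest cost in precision. The article's own text means that patients randomised before or without repair are pooled with patients randomised after it. The stratification, the primary test and the wording of the objective and conclusion all ignore the difference.

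The post-operative share is about 44–90% of participants if the registry's surgical share applies and half to all surgical patients enter after repair. Even the low end is 167 of 384. Adjustment would remove about 4–8% of outcome variance under the two assumed mortality splits; nothing in the article shows how strongly entry status predicts death.

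The comparison between arms remains valid for those enrolled. The effect of late entry on the 27.4% control mortality, and so on power, is a separate matter and is not counted here.

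**What to change.** 1. Record, before the allocation envelope is opened, whether aortic repair has already been done, and the time from symptom onset and from admission. For participants already enrolled, back-fill these from the chart. They are dated facts that precede allocation, although onset times may be less exact.
2. Replace the unadjusted chi-square as the primary mortality comparison with one adjusted for operative status at randomisation together with the type A/B stratum. Specify it before database lock.
3. Report the effect descriptively by operative status, with the number of patients and deaths in each group. The trial is not sized for a test of interaction.
4. Word the objective, and the conclusion in Limitations and Discussion, as in-hospital death within 30 days of randomisation among AAD patients able to take oral medication, including those enrolled after repair.

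The cost is two case report form fields, one extra covariate and a narrower conclusion. No treatment, eligibility or other clinical rule changes.
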